#### Secondary outcomes

The secondary outcomes include urinary protein creatinine ratio, serum creatinine level, biochemical test, cardiovascular function, quality of life and endpoint events (Table 1).

**Table 1 Tab1:**
[figure not shown]
Schedule of study

The urinary protein creatinine ratio will be examined at baseline, and at 3, 6, 9 and 12 months. Serum creatinine level (SCr) and blood urea nitrogen level (BUN) will be measured at baseline, and at 1, 2, 3, 6, 9, and 12 months. Biochemical tests including plasma albumin, triglyceride, cholesterol, calcium, phosphate, and intact parathyroid hormone level (iPTH) will be measured at baseline, and at 3, 6, 9, and 12 months.

We will assess the patient's cardiovascular function by left ventricular ejection fraction (LVEF), interventricular septal thickness (IVST), left ventricular posterior wall thickness (LVPWT), carotid artery intima-media thickness (CIMT) through the Carotid Doppler and Cardiac Doppler, which will be measured at baseline and 12 months.

The Kidney Disease Quality of Life Instrument (KDQOLSF 1.3) scale will be evaluated at baseline and at 6 and 12 months.

Endpoint events are defined as serum creatinine level increasing to double the baseline level, ESRD (requiring permanent dialysis or kidney transplantation), cardiovascular or cerebrovascular events (acute myocardial infarction, heart failure, ischemic cerebral infarction or cerebral hemorrhage verified by typical clinical manifestations, electrocardiogram (ECG) alterations, and imaging and laboratory investigations) or death. The nature and severity of events will be recorded as endpoint events during the follow-up period.

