## Background

The high incidence of chronic kidney disease (CKD) and associated poor outcomes presents a major public health problem in many developed countries. The prevalence of CKD ranges from 9.4 to 13.0 % in China [1, 2], which is similar to the reported prevalence in North America [3, 4] and Australia [5].

Patients with CKD are at a high risk of cardiovascular events and can gradually develop end stage renal disease (ESRD), with a decreasing estimated glomerular filtration rate (eGFR) of 2 to 20 ml/min/1.73 m^2^ per year [6]. Patients with ESRD require renal replacement therapy to maintain their life, and the rising prevalence of CKD represents an increasing economic burden to many countries. For example, in Taiwan, only 7.7 % of those over the age of 65 are diagnosed with CKD, but 15.9 % of the national health care expenditure is spent treating this condition [7].

The current treatments applied to delay the progression of CKD are limited and only partially effective. Angiotensin-converting enzyme inhibitors (ACEi) and angiotensin receptor blockers (ARBs) are recommended for their antihypertensive and proteinuria-reducing effects [5]. However, ACEi or ARBs can only reduce the risk of ESRD by 50 % [8]. The risks of adverse events including hyperkalemia and acute kidney injury limit the application of ACEi/ARBs in advanced CKD (stages 4 and 5) and elderly patients [9]. Aside from ACEi/ARB and complication management, there are no effective treatments for advanced CKD [5]. Thus, a novel, economical and effective intervention is urgently sought.

In China, Chinese medicine (CM) is widely applied for CKD and an evidence-base application of CM is gradually accumulating. Several large clinical studies have indicated benefit effects of Chinese herbal medicine in early stage CKD patients [10, 11]. However, CM interventions for stage 4 CKD populations are lacking, and further investigations are required to evaluate the risks and benefits of CM in this subgroup population.

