An analysis of covariance will be used for continuous variables, and the Cochran–Mantel–Haenszel test will be used for categorical variables to adjust for the center effect. Unconditional logistic regression analysis will be used for the curative effect factors analysis. The Kaplan–Meier method will be used to assess the incidence and mean occurrence time of endpoint events. Cox proportional hazards regression will be used to analyze factors influencing the incidence of endpoint events. Subgroup analysis of risk factors including hypertension, proteinuria will be performed. The Fisher exact test will be used to compare the incidence rates of AEs and adverse drug reactions over the course of treatment.

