### Termination and withdrawal

Patients failing to complete the clinical observation will be classified as case dropouts. Investigators will contact these patients and attempt to record the reason for dropping out and the last time they took the studied medicine. Participants will be withdrawal from the study in any of the following situations: 1) commencing permanent renal replacement therapy (dialysis >30 days or kidney transplantation); 2) severe infection, hyperkalemia (K^+^ > 6.5 mmol/L), acidosis (TCO_2_ < 13 mmol/L), or heart failure not curable by medication, deterioration of kidney function that demands dialysis, massive hemorrhage of the gastrointestinal tract, serious arrhythmia dependent on anti-arrhythmic drugs, or uremic encephalopathy; 3) severe primary disease such as an active-stage malignant tumor, decompensating liver cirrhosis, or hematopoietic system disease; 4) urinary tract obstruction that requires surgical treatment; 5) death; 6) withdrawal of consent; 7) transfer to a renal unit which is not an active study site.

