### Quality control and compliance improvement

This trial will be monitored by contract research organization program managers from, Guangdong International Clinical Research Center of Chinese Medicine (Guangzhou, China), contracted by the research sponsor. The program manager and their team will visit each site to examine trial procedures, ensure data quality, and monitor compliance with the protocol. A data safety monitoring board, consisting of seven independent members, will be established to assess safety events, primary outcomes, and data quality. The department of science research of Guangdong Provincial Hospital of Chinese Medicine will be responsible for trial auditing and inspection for the study.

Measurement of eGFR will be delivered in accordance with the protocol. The investigators will attend a 3-hour training workshop on the protocol and will be provided with a protocol and relevant SOPs. The detection of SCr used to estimate eGFR will be standardized at all sites. All sites will be requested to use the same method, procedure, and reagent when performing SCr detection. The precision performance of SCr will be evaluated using the guidelines in the CLSI Document EP15-A2 published in 2005 by American Clinical and Laboratory Standards Institution (CLSI) [26]. The laboratory method of SCr concentration detection at each site will be validated with a standard substance and will only be accepted if the SCr coefficient of variation is between 1.0 % and 3.0 %.

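### The creatinine-doubling component of the secondary endpoint-event composite has no persistence condition, so reversible rises may count as progression, plausibly more often on losartan

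*Protocol article*

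**What the plan says.** Protocol article, Outcome measurements, Secondary outcomes (text below Table 1): "Endpoint events are defined as serum creatinine level increasing to double the baseline level". The same sentence adds "ESRD (requiring permanent dialysis or kidney transplantation"), then cardiovascular or cerebrovascular events, then death. The vascular events must be verified by clinical picture, ECG, imaging and laboratory work.

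Termination and withdrawal gives a duration for dialysis: "commencing permanent renal replacement therapy (dialysis >30 days or kidney transplantation").

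Serum creatinine "will be measured at baseline, and at 1, 2, 3, 6, 9, and 12 months". The article describes no repeat or confirmatory sample.

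On the comparator class, the Background says: "The risks of adverse events including hyperkalemia and acute kidney injury limit the application of ACEi/ARBs in advanced CKD" (stages 4 and 5) and in elderly patients.

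The composite is one of several secondary outcomes ("quality of life and endpoint events (Table 1"). Under Statistical analyses, the Kaplan–Meier method "will be used to assess the incidence and mean occurrence time of endpoint events", and Cox regression examines the factors that influence it.

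**The concern.** A doubling of creatinine is meant to stand for lasting loss of kidney function, but creatinine can also rise and come back down. The definition has nothing that separates the two. In a Kaplan–Meier or Cox analysis of time to first event, a patient who reaches twice baseline at month 1 and recovers by month 2 stays counted as an event.

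The two arms may not be equally exposed to this. One arm takes losartan and the other takes losartan placebo, and both are advised against any other ACEi or ARB. Creatinine is sampled at months 1 and 2, when an early drug-related rise would be seen. If such rises reach a doubling, a safety effect of the comparator would enter the efficacy comparison as slower progression under BYF. The Conclusions section says that the trial will assess whether BYF lowers the incidence of these events, so the composite will be used for a claim.

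The safety section is not an evident second route for these rises. It defines adverse events as symptoms, and creatinine is not among the safety laboratory tests that it names.

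**Working it through.** **1. The plan's own figure.** The only sample-size figure is for eGFR change. The inputs are in Sample size calculation: declines of 4.5 and 6.8, SD 4.2, margin 1, one-sided 2.5%, power 90%.

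- Difference beyond the margin: 6.8 − 4.5 − 1 = 1.3.
- n = 2 × (1.960 + 1.282)² × 4.2² / 1.3² = 219.4, so 220. The t-test version gives 221, as stated.
- 221 / 0.80 = 276.25, so 277, as stated.

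No input is an event rate. The definition of doubling therefore cannot change 221 or 277.

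**2. The components side by side.**

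| Component | Condition stated |
|---|---|
| Creatinine doubling | none beyond reaching the level |
| ESRD | permanent dialysis or transplantation; more than 30 days in the withdrawal section |
| Vascular events | verified by clinical, ECG, imaging and laboratory findings |

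**3. Can assay error produce a doubling?** Each site's method "will only be accepted if the SCr coefficient of variation is between 1.0 % and 3.0" %. The ratio of two values with CV 3% has a CV of about √2 × 3% = 4.2%, against a required rise of 100%. Assay error is not the issue; only a real but reversible rise is.

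**4. Rough scale of true doublings.** This needs two assumptions that the document does not give: eGFR varies as creatinine to the power −1.209, and 12-month declines are normal with SD 4.2 in both arms.

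- At doubling, eGFR is 2^−1.209 = 0.433 of baseline, a loss of 0.567 × baseline.
- Baseline 22.5 (assumed, about mid-range): loss 12.8. P(decline > 12.8) is 2.5% with mean 4.5 and 7.8% with mean 6.8, or about 7 and 22 of 277.
- Baseline uniform over 15 to 29.9: 4.5% and 11.2%, or about 12 and 31 of 277.

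The 6.8 is a median from a benazepril trial and the SD comes from the CM series alone, so these are orders of magnitude only. They suggest that doublings number in the single figures to low tens per arm.

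**5. What transient doublings could do (illustration).** Assume the same true composite event rate p in both arms, 277 per arm, and transient doublings in an extra fraction q of otherwise event-free losartan patients only. Then the losartan rate is p₂ = p + (1 − p)q, the extra events are 277(p₂ − p), and the apparent risk ratio is p/p₂. The chance of a significant result favouring BYF (two-sided 5% test of proportions) is Φ[(p₂ − p − 1.96·se₀)/se₁], with se₀ pooled and se₁ unpooled.

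Example, p = 10%, q = 2%: p₂ = 0.10 + 0.90 × 0.02 = 0.118; se₀ = √(0.109 × 0.891 × 2/277) = 0.0265; se₁ = √[(0.0900 + 0.1041)/277] = 0.0265; Φ[(0.018 − 0.0519)/0.0265] = 0.100.

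| p | q | p₂ | Extra events | Risk ratio | Chance of false result for BYF |
|---|---|---|---|---|---|
| 5% | 1% | 5.95% | 2.6 | 0.84 | 0.071 |
| 5% | 2% | 6.90% | 5.3 | 0.72 | 0.155 |
| 5% | 5% | 9.75% | 13.2 | 0.51 | 0.571 |
| 10% | 1% | 10.9% | 2.5 | 0.92 | 0.053 |
| 10% | 2% | 11.8% | 5.0 | 0.85 | 0.100 |
| 10% | 5% | 14.5% | 12.5 | 0.69 | 0.365 |

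With q = 0 the risk ratio is 1.0 and the chance is the nominal 0.025. The values of p and q are all assumed.

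**The case against.** A reader might infer that the protocol lets a single unconfirmed value count. It does not say so; that reading comes from silence. This is a condensed article, a separate statistical analysis plan is announced, and SOPs are mentioned. A confirmation rule could stand in any of them, and nothing in the article contradicts one. That is a fair limit on certainty. What remains is that the article gives a formal definition, qualifies the neighbouring components in the same sentence, and leaves this one bare.

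A reader might also infer that the comparison is biased against losartan. The article does not show that. It gives no kidney-injury rate for either arm, no evidence that ARB-related injury reaches a doubling, and no figures that put the rate lower under BYF. If transient doublings were equally common in both arms, there would be no bias under the null. The direction is plausible and the size unknown.

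There are partial safeguards. The trial is blinded, patients with GFR fluctuating by more than 30% before enrollment or with hyperkalemia are excluded, the assay is standardised, and serial creatinine is reported separately, so a reversal would be visible. These limit differential ascertainment, unstable baselines and assay noise. They do not remove a real, transient drug effect after randomization.

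Finally, a confirmation rule can itself lose true events. Months 1 and 2 are only about 30 days apart, so a rule of strictly more than 30 days could fail there. Patients withdrawn for deteriorating kidney function may never have a confirming value. Both points stand, and the fix has to deal with them.

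**Conclusion.** The concern holds in a limited form. As written, the creatinine component is met on reaching twice baseline, without persistence, while the ESRD component must be permanent. Reversible rises may therefore be counted as progression, plausibly more often on losartan, given the class risk that the Background itself names.

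The size cannot be computed from the document. The illustrated risk ratios of 0.92 to 0.69 (10% event rate) and 0.84 to 0.51 (5% event rate) rest wholly on an assumed 1% to 5% of transient doublings confined to the losartan arm. They show that a few spurious events could matter, not that they will occur.

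The reach is one component of one secondary composite. The primary outcome, change in eGFR, and the 221/277 sample size do not depend on it. The change is still worth making, because it is nearly free and brings this component closer to the persistence standard already applied to dialysis.

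**What to change.** Replace the creatinine component with a confirmed one:

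- **Event:** creatinine at least twice baseline, confirmed at the next scheduled creatinine visit (about four weeks or more later) and dated to the first value.
- **Clinical outcome before confirmation:** a doubling followed by ESRD, death or withdrawal for deteriorating kidney function before the next visit counts as an event.
- **No later value:** doublings first seen at month 12, or otherwise without a later creatinine, count in the main analysis. A sensitivity analysis excludes them.
- **Not confirmed:** report by arm as kidney safety events.
- **Second sensitivity analysis:** the composite with any single value at twice baseline.

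If the full protocol or the analysis plan already holds such a rule, it is enough to state it with the definition.

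The cost is a few sentences and slightly fewer events. The schedule already has creatinine at months 1, 2, 3, 6, 9 and 12, so no extra sample is needed, and the sample size does not change.

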### Safety evaluation

Participants will be asked to report all adverse events (AEs) at each follow up. AEs are defined as any symptom occurring during the intervention period [24]. Expected AEs include dizziness, diarrhea and thirst. Where AEs are reported, clinicians will provide the appropriate treatment in accordance with the study standard operative procedures (SOPs). Laboratory examinations, including routine blood test, urine and stool tests, serum potassium, liver function (AST, ALT), will be monitored at baseline, 3, 6, 9 and 12 months. Serum potassium concentration will be closely monitored at each month. ECG will be reviewed every six month. All AEs will be classified by investigator based on treatment, involving system, severity and temporal correlation with interventions.

Any serious adverse events (SAEs) will be reported, recorded and treated within 24 hours, and reported to the principle investigator and ethics committee for causality assessment. The causality assessment for AEs will be performed according to the WHO-UMC standard [25].

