*Bupi Yishen* formula (BYF), a Chinese herbal compound, was developed from the classical Chinese prescription Sijunzi decoction, and was modified according to data mining 10,000 CKD stage 4 outpatient records. BYF exhibited a potential renal protective effect in preliminary unpublished observational studies. Twenty-six CKD stage 4 patients were treated with BYF orally once a day based on conventional western therapy. After one-year, eGFR decline was observed in 17 of 26 patients, with a mean reduction of 2.39 (mean: 2.39, standard deviation: 5.59). The decline of eGFR was slower than 6.8 ml/min/1.73 m^2^ per year receiving benazepril in patients with CKD stage 4 that observed in Hou’s study [12].

Components of BYF include *Astragalus mongholicus* (Huangqi), *Codonopsis pilosula* (Dangshen), *Macrocephalae* (Baizhu), *Poria cocos* (Fuling), *Rhizoma dioscoreae* (Shanyao), *Semen coici* (Yiyiren), *Radix polygoni multiflori* (Heshouwu), *Semen cuscutae* (Tusizi), and *Salvia miltiorrhiza* (Danshen). Some of these components have been reported to reduce proteinuria, inhibit renal fibrosis and improve renal function in experimental studies [13–16]. Based on this evidence, a trial was designed to assess the efficacy and safety of BYF for delaying progression in patients with non-diabetes stage 4 CKD. The efficacy of BYF was compared with an Angiotensin II antagonist, Losartan.

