### Inclusion and exclusion criteria

The participant inclusion criteria are as follows: age from 18 to 80 years; diagnosed with stage 4 CKD at least 3 months prior to enrollment; blood pressure below 140/90 mmHg.

The participant exclusion criteria are as follows: imminent initiation of renal replacement therapy; current corticosteroid or immunosuppressive therapy; serious arrhythmia, heart failure (New York Heart Association Functional Classification stage 4), myocardial infarction, unstable angina, or cerebrovascular accident; concomitant diabetes, malignant tumor, hepatitis B, decompensating liver cirrhosis, active tuberculosis, acute infectious disease contributing to CKD progression, or any condition (mental or physical) that would interfere with participants’ ability to comply with the study protocol; GFR fluctuated by more than 30 % within the 3 months prior to enrollment; hyperkalemia (serum potassium level higher than the upper reference interval limit); history of allergy to any component of the interventions; pregnant or lactating; enrolled in another clinical trial.

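### Adverse events are defined as symptoms only, so silent hyperkalaemia, liver enzyme rises and ECG changes need not be counted, graded or compared by arm as adverse events

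*Protocol article*

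**What the plan says.** All references are to the protocol article.

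- **Definition (Safety evaluation).** "AEs are defined as any symptom occurring during the intervention period". Events are collected by asking participants to report them at each follow-up, and the expected events listed are dizziness, diarrhoea and thirst, all of them symptoms.
- **Tests (same section).** "Serum potassium concentration will be closely monitored at each month"; "liver function (AST, ALT), will be monitored at baseline, 3, 6, 9 and 12 months"; ECG is reviewed every six months.
- **What is done with adverse events.** "All AEs will be classified by investigator based on treatment, involving system, severity and temporal correlation with interventions", and "The causality assessment for AEs will be performed according to the WHO-UMC standard". Statistical analyses assigns a Fisher exact test to the incidence of adverse events and adverse drug reactions.
- **Potassium elsewhere.** Inclusion and exclusion criteria rules out "hyperkalemia (serum potassium level higher than the upper reference interval limit") at entry. Termination and withdrawal lists potassium above 6.5 mmol/L.
- **Aim and comparator.** The Background says "a trial was designed to assess the efficacy and safety of BYF", and of the comparator's class: "The risks of adverse events including hyperkalemia and acute kidney injury limit the application of ACEi/ARBs in advanced CKD". The control arm takes losartan 100 mg daily.

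**The concern.** The definition is a stated rule, not a detail left to another document, and it is too narrow for this trial. Important harms that can be expected here are laboratory findings. Hyperkalaemia is the class risk that the article itself names, and liver enzymes are monitored over a year's exposure to a nine-herb compound. A patient cannot report a silent rise in potassium or ALT.

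A site that follows the wording need not record such results as adverse events, so they would receive no severity or causality grade and would not enter the planned between-arm comparison. The bias can run either way: under-counting hyperkalaemia on losartan would hide a possible safety advantage of BYF, and under-counting silent liver enzyme rises would hide a harm in either arm. Sixteen centres may also interpret the word differently, which makes the counts uneven between sites.

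**Working it through.** **1. Reading the rule through the article**

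| Finding without symptoms | Measured? | Adverse event as defined? | Caught elsewhere? |
|---|---|---|---|
| Potassium above upper reference limit, up to 6.5 mmol/L | Yes, monthly | No | No |
| Potassium above 6.5 mmol/L | Yes, monthly | No | Withdrawal criterion |
| ALT/AST above upper limit | Yes, months 3, 6, 9, 12 | No | No |
| ECG abnormality | Yes, six-monthly | No | Only if part of a cardiovascular endpoint event or a serious arrhythmia dependent on drugs |
| Decline in kidney function | Yes | No | Yes: eGFR (primary), serum creatinine (secondary), creatinine doubling (endpoint event) |

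Potassium above the upper limit is excluded at entry, so a value in the first row is new on study. The withdrawal sentence is ambiguous: its qualifier about failure of medication may also apply to hyperkalaemia, in which case even values above 6.5 mmol/L would not always lead to withdrawal. Kidney function is well covered; only its classification as an acute adverse event is missing.

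**2. Illustration of size**

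The article gives no figure to reproduce, no hyperkalaemia rate and no symptomatic share. Inputs:

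- From Sample size calculation: n = 277 per arm randomised, or 221 per arm after 20% loss.
- Assumed: true proportion with potassium above the upper limit (up to 6.5 mmol/L) of 10% on losartan and 5% on BYF, or 20% and 10%.
- Assumed: share of cases with symptoms, f, of 50%, 25% or 10%; f = 100% represents all cases counted.

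Formulas: total cases = n × (p_losartan + p_BYF); cases not counted = total × (1 − f); counted proportion in each arm = f × p. Power is that of the exact two-sided Fisher test at 5%, summed over both binomial distributions.

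Example, n = 277, 10% and 5%, f = 50%: total = 277 × 0.15 = 41.6; not counted = 41.6 × 0.5 = 20.8; counted proportions 5% and 2.5%; power 27.0%.

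| n per arm | True rates | Total cases | Not counted (f = 50 / 25 / 10%) | Power, all counted | Power (f = 50 / 25 / 10%) |
|---|---|---|---|---|---|
| 277 | 10% vs 5% | 41.6 | 20.8 / 31.2 / 37.4 | 55.0% | 27.0 / 10.9 / 1.8% |
| 277 | 20% vs 10% | 83.1 | 41.6 / 62.3 / 74.8 | 89.7% | 55.0 / 27.0 / 8.0% |
| 221 | 10% vs 5% | 33.2 | 16.6 / 24.9 / 29.8 | 45.2% | 20.3 / 7.9 / 0.9% |
| 221 | 20% vs 10% | 66.3 | 33.2 / 49.7 / 59.7 | 81.2% | 45.2 / 20.3 / 5.4% |

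The table treats hyperkalaemia as one adverse event type tested on its own. The article specifies a Fisher test on adverse event incidence without saying whether it is done by type, so these figures only show how the definition thins the count.

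**The case against.** The best reply is that one word carries the point and may be loose drafting. The section moves from the definition to the tests and then to classification, which fits test results feeding into adverse events, and the Background uses the term adverse events for hyperkalaemia and acute kidney injury. The definition cites a reference that is not shown, event handling follows study procedures that are not shown, and the rules for when a laboratory value becomes an adverse event often sit in the full protocol. Laboratory tables by arm are ordinary SAP content. A seven-member monitoring board, 24-hour reporting of serious events, the withdrawal criteria and the endpoint events guard against serious harm. The illustration rests wholly on assumed rates.

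Much of this is fair. A broader intention is plausible, the power figures are not evidence from this trial, and the absence of a laboratory table would be no fault by itself. The results are collected in both arms, and the general categorical tests in Statistical analyses could be applied to them; efficacy is untouched. None of this removes the point. The article fixes a definition, and collection by patient report and the list of expected events agree with its narrow reading. The Background wording is not a competing definition. The safeguards cover serious cases, not the non-serious silent abnormalities at issue.

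**Conclusion.** The concern holds. As written, the definition leaves out asymptomatic potassium between the upper reference limit and 6.5 mmol/L, asymptomatic ALT/AST rises and asymptomatic ECG abnormalities from adverse event counting, grading, causality assessment and the planned between-arm comparison. That follows from the text and does not depend on any rate.

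The size is uncertain. Under the assumed range, half to nine-tenths of hyperkalaemia cases go uncounted, simply because 50% to 10% were assumed symptomatic, and the power to see a doubling on losartan falls accordingly. The loss is confined to the adverse event analysis, since the measurements exist. This should be corrected because safety is a stated aim and the correction is cheap; it does not threaten the primary result. Confidence is medium, because the full protocol may already use a wider definition.

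**What to change.** Define an adverse event as any untoward medical occurrence after the first dose, whether or not symptomatic, including clinically significant laboratory or ECG abnormalities. If that was always intended, the one sentence needs correcting and the sites need telling.

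Also report by arm the number of patients with potassium above the upper reference limit and above 6.5 mmol/L, the two thresholds the protocol already uses, and with ALT/AST above the upper limit. These tables can be specified in the SAP, before unblinding.

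Cost: one reworded definition, a few tables and no new measurements. The trial is already recruiting, but the tables can still be built from scheduled data. The drawback is more adverse events for sites to record and grade.
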